### Control groups

Two control groups will be recruited. The first control group will consist of non-malnourished children who are recruited at the same age (11 months to 13 months old) as the MAM intervention group children.

The second control group (i.e. outcome reference group) will be a MAM reference group consisting of children who are 3 years (34 months to 38 months old) who present with previously untreated MAM. See Fig 2 demonstrating the flow of recruitment process of the study participants.

**Fig 2 pone.0296529.g002:**
[figure not shown]
Flow chart of the study settings and participants.

### Sample size

Power for comparisons between well-nourished (WLZ/WHZ > -1 SD) and wasted children (-3≤ WLZ/WHZ <-2 z-score, and/or 11.5≤ MUAC <12.5 cm) at 1 and 3 years was estimated using the Student’s t-test and Structural Equation Modeling (SEM). For the t-test, the proposed medium level difference between the two groups (i.e. 2 standard deviation) requires a minimum of 51 participants per group for power equal to 80% using a level of significance equal to 5% (for a one-tailed test).

Sideridis et al. 2014 [23] used a series of Monte Carlo simulations to estimate that 50–70 participants would suffice to evaluate functional connectivity in the brain using EF, EEG or fMRI. Sideridis et al.’s simulation involved medium sized models (i.e. 7 latent variables), but the model size is inversely related with sample size. Therefore, larger models, like those in the present study, require fewer participants.

To account for participant drop out during the follow-up period, sample sizes were increased to n = 70 children in each group.

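### The sample-size section gives the target difference as 2 SD, but 51 per group is the requirement for 0.5 SD

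*Protocol article*

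**What the plan says.** The Sample size section of the protocol article sets out a power calculation. It concerns well-nourished versus wasted children at 1 and 3 years: "Power for comparisons between well-nourished (WLZ/WHZ > -1 SD) and wasted children". Power "was estimated using the Student’s t-test and Structural Equation Modeling (SEM").

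For the t-test part, the section says that the proposed "medium level difference between the two groups (i.e. 2 standard deviation) requires a minimum of 51 participants per group". The power is 80%, and the error rate is a "level of significance equal to 5% (for a one-tailed test"). The groups are then raised from 51 to 70 for drop-out.

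The same section also cites published simulations suggesting that 50–70 participants suffice for the structural equation modelling. That argument gives no effect size, power or significance level. Nothing else in the article states a detectable difference or an outcome standard deviation.

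**The concern.** The sentence contradicts itself. A difference of 2 SD between two group means is very large and would not usually be called medium, and a t-test needs only a handful of children per group to detect it. A requirement of 51 per group points to a much smaller effect.

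This is the article's only statement that ties a detectable effect to power and a significance level. Taken at face value, it misleads in one of two ways. Either the study appears to be designed to find only a 2 SD gap between well-nourished and wasted children, or 51 to 70 per group appears to be far more than its stated aim needs. Both misdescribe what the study can detect.

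**Working it through.** **Inputs, all from the Sample size section**

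- Test: two-sample Student's t-test with equal groups
- Significance level: 5%, one-tailed
- Power: 80%
- Stated effect: d = 2 (difference divided by SD)
- Stated result: 51 per group

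**Step 1. Normal approximation**

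n per group = 2 × (z₀.₉₅ + z₀.₈₀)² / d² = 2 × (1.645 + 0.842)² / d² = 12.37 / d²

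- d = 2: 12.37 / 4 = 3.09, so 4 per group
- d = 0.5: 12.37 / 0.25 = 49.5, so 50 per group

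**Step 2. Exact t-test**

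Power = P(T > t₀.₉₅), where T is noncentral t with 2n − 2 degrees of freedom and noncentrality d × √(n/2).

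| d | n per group | df | Critical value | Noncentrality | Power |
|---|---|---|---|---|---|
| 2 | 3 | 4 | 2.132 | 2.449 | 64.5% |
| 2 | 4 | 6 | 1.943 | 2.828 | 80.2% |
| 2 | 5 | 8 | 1.860 | 3.162 | 89.2% |
| 0.5 | 50 | 98 | 1.661 | 2.500 | 79.9% |
| 0.5 | 51 | 100 | 1.660 | 2.525 | 80.6% |

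With the inputs as printed, the plan's figure of 51 is not reproduced: the answer is 4. At d = 2, power with 51 per group is essentially 100%. With d = 0.5 and nothing else changed, the exact solution is n = 50.15, which rounds up to 51, the plan's own figure.

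**Step 3. Solve the other way**

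The smallest difference that 51 per group detects with 80% power, one-tailed at 5%, is 0.496 SD by the exact t-test. The normal approximation gives √(12.37/51) = 0.492 SD.

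**Step 4. Could a different choice of sides rescue 2 SD?**

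No. Two-sided at 5%, d = 2 needs 4 per group by the normal approximation and 6 by the exact t-test.

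**Step 5. Size of the discrepancy**

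- Effect: 2 / 0.5 = 4-fold
- Sample size: 51 / 4 = 12.75-fold

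**Step 6. Dependence on the one-tailed test**

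At d = 0.5, a two-sided 5% test needs 64 per group (exact t), and 51 per group would give 70.6% power. If all 70 per group were retained, power at 0.5 SD would be 90.3% one-tailed and 83.6% two-sided.

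**The case against.** The best reply is that this is a slip in one figure and not a design error. Every other element of the sentence agrees with 0.5 SD. A fraction such as one half may have been lost in typesetting or when the text was read from the PDF. Correcting it changes no group size, test or analysis. The simulation-based range of 50–70 also supports the chosen numbers independently. Finally, a null result is read from its estimate and interval, not from a planning assumption, and this calculation does not cover the randomized comparison of Group A with Group B at all.

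Much of this stands. The cause may well be a lost fraction, the number enrolled fits 0.5 SD, and this is not the section's only numerical argument. The effect on reading a null result is limited, and is confined to the comparison of well-nourished with wasted children.

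It does not remove the error. The printed figure is wrong, it sits in the sentence that defines what the study can detect, and the article gives nothing else from which to correct it. The parenthesis reads as complete, with no visible gap. Nor can 2 SD be read as the separation in weight-for-length between the groups, because the sentence presents it as the difference that requires 51 per group.

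**Conclusion.** The concern holds. The stated 2 SD is incompatible with 51 per group at 80% power and a one-tailed 5% level. It would need 4 per group, whereas 51 is exactly the requirement for 0.5 SD. The stated effect is therefore too large by a factor of four, while the sample size itself is consistent with a medium effect of 0.5 SD.

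The conclusion assumes equal groups, a common SD and the two-sample t-test that the section names. That 0.5 SD was the intended value is an inference from the exact match and the word medium. It is strong, but the sponsor should confirm it. The error lies in the description of the target effect; it does not show that the trial is too small for that comparison under the one-tailed test stated.

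**What to change.** In the Sample size section, replace 2 standard deviation with 0.5 standard deviation, after checking it against the original power calculation. Keep the one-tailed qualifier next to it, since 51 per group is correct for 0.5 SD only under that choice.

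The cost is one corrected figure. The 51 and 70 per group stay as they are, with no more children and no change to the design or analysis.

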### Data analysis plan

The study will result in a rich data set consisting of neuropsychological assessments of executive functions and emotion regulation, blood nutriome and metabolome, microbiomes, genetics, nutritional status, age, sex, DOB, demography and SES from family, medical history of these children.

Statistical tests will be conducted to quantify differences in the neurocognitive assessments (e.g. EF, NIRS and EEG responses) between and within the wasted and non-malnourished cohorts, all of whom have varied levels of exposure to adversities (single adversities, composite exposure scores, and income). Three model types will be employed, (a) a t-test for analyzing univariate outcomes, (b) linear mixed models, and (c) structural equation modeling to analyze multivariate outcomes.

T-tests will be conducted with an alpha level of 5% and the distributions of the two samples will be checked for normality, homogeneity of variances and autocorrelation in the residual terms. The False Discovery Rate (FDR) method will be applied to correct for potential multiple comparisons.

Linear mixed effects model will be used to evaluate longitudinal effects with respect to the group differences and the relationship with other earlier biological and/or psychosocial risk factors, particularly focusing on the brain power and functional change in development. Since these measurements are repeated at three time points, mixed models with either random intercept or random slope will be considered.

Structural equation modeling will be used to evaluate multivariate relationships. Model fit will be evaluated using descriptive fit indices such as the Comparative Fit Index (CFI) which work with relatively small sample sizes (Bentler et al, 1990) [50].

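### The 80% power at 51 per group is for one uncorrected one-tailed 5% t-test, but the analysis plan applies FDR correction over several outcomes and leaves sidedness unstated

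*Protocol article*

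**What the plan says.** The Sample size section of the protocol article powers a comparison of well-nourished with wasted children at 1 and 3 years. For the t-test, "the proposed medium level difference between the two groups (i.e. 2 standard deviation") is said to need at least "51 participants per group for power equal to 80% using a level of significance equal to 5% (for a one-tailed test"). It makes no allowance for multiple testing. The increase from 51 to 70 per group is attributed to drop-out alone, and no drop-out rate is given.

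In the Data analysis plan, "Statistical tests will be conducted to quantify differences in the neurocognitive assessments", with EF, NIRS and EEG responses as examples. The t-tests use a 5% alpha and no sidedness is given. The plan then adds: "The False Discovery Rate (FDR) method will be applied to correct for potential multiple comparisons". No outcome is named as tested outside that correction.

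**The concern.** The test used to size the trial is not the test the analysis plan describes. The sizing takes one t-test at an unadjusted one-tailed 5%. The analysis takes several t-tests whose p-values are adjusted before any is declared significant. A sample that just reaches 80% for the first falls short for the second.

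The 80% figure is what a reader uses to interpret a null result. If true power at 51 completers is materially lower, a non-significant difference would be given more weight as evidence of no difference than it deserves. The silence on sidedness adds to this, because the 51 depends on a one-tailed test and the analysis plan neither confirms nor rejects one.

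**Working it through.** **Inputs.** From the Sample size section: 51 per group, 80% power, 5% one-tailed, 70 recruited per group. From the Data analysis plan: 5% alpha, FDR correction, several outcomes. Assumed because not stated: equal groups; Benjamini–Hochberg at q = 0.05 as the FDR method; the number of tests m, their correlation, and how many carry a true effect.

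**Effect size.** The section calls the difference medium but prints 2 SD. Under a one-tailed 5% test, 2 SD would need about 4 per group. Only d = 0.5 gives 51, so d = 0.5 is used throughout. The printed 2 SD is a separate inconsistency.

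**Reproducing 51.** For a two-sample t-test, noncentrality = d × √(n/2), with 2n − 2 degrees of freedom.
- n = 51: 0.5 × √25.5 = 2.525, df = 100, one-tailed critical t = 1.660, power **80.6%**.
- n = 50: power 79.9%. So 51 is the minimum, with 0.6 points to spare.

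**If the tests are two-sided, before FDR.**
- n = 51: critical t = 1.984, power **70.6%**.
- n = 70: noncentrality 0.5 × √35 = 2.958, power **83.6%** (one-tailed 90.3%).
- 80% needs 64 per group (80.1%; n = 63 gives 79.5%). From 70 that allows a loss of 1 − 64/70 = 8.6%, against 1 − 51/70 = 27.1% under the stated minimum.
- Difference detectable with 80% power: 0.56 SD at 51 and 0.48 SD at 70.

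**Direction of the FDR effect.** The Benjamini–Hochberg adjusted p-value of the i-th smallest p is the minimum over j ≥ i of m × p(j)/j. Since m/j ≥ 1 and p(j) ≥ p(i), it is never below the raw p(i). Correction therefore cannot raise power, and the slack is only 0.6 points.

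**Size of the FDR effect.** Simulated average power per true effect, d = 0.5, one-tailed, independent tests:

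| Tests m | n = 51, one true | n = 51, all true | n = 70, one true | n = 70, all true |
|---|---|---|---|---|
| 2 | 71% | 79% | 84% | 89% |
| 5 | 58% | 77% | 73% | 89% |
| 10 | 47% | 77% | 64% | 89% |
| 20 | 38% | 77% | 55% | 89% |

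An illustrative family of six takes the three tasks in the Executive functions section at the two ages in the Sample size section. With an assumed correlation of 0.3 and 1, 3 or 6 true effects:

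| | n = 51 | n = 70 |
|---|---|---|
| One-tailed | 54 / 66 / 76% | 71 / 81 / 88% |
| Two-sided | 45 / 55 / 64% | 62 / 72 / 80% |

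These are simulation results, good to about one point.

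**The case against.** Several counter-arguments are sound and limit the point.

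- **Sidedness is not contradicted.** The Data analysis plan never says two-sided, and speaking of differences does not settle it. A reader might infer that the analysis is two-sided and that the sizing is wrong for that reason. The text does not support this: the two-sided figures are conditional, and the FDR mismatch stands under one-tailed tests too.
- **The family is not defined.** The article refers only to potential multiple comparisons, and the family is a detail that a full protocol or analysis plan may hold. Six tests and a correlation of 0.3 are illustrations. With independent tests and a true effect behind every one, the one-tailed loss at 51 is only about 1 to 4 points, and it would vanish if such tests were also almost perfectly correlated.
- **51 is a floor, not a forecast.** The plan recruits 70 per group. The 1-year comparison is made at enrolment, before any drop-out, so 70 is the relevant number there. A reader might infer that 80% is out of reach in every case. It is not: at 70 per group, one-tailed, the six-test illustration gives 81% with three true effects and 88% with six. Pooling both MAM arms would also help (51 against 102 gives 89.6% one-tailed, uncorrected), although the article states its minimum per group and does not describe pooling.
- **The two feeds.** A reader might infer that a one-tailed rule would prevent the trial from showing that the enhanced feed is worse. The one-tailed test is attached to well-nourished versus wasted children, a contrast with a natural direction. Nowhere is it applied to Group A versus Group B.

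What remains is that the article itself presents 51 as sufficient for 80% and itself commits to a correction which that figure ignores.

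**Conclusion.** The point holds in this limited form. The stated 80% at the stated minimum of 51 belongs to one uncorrected one-tailed 5% t-test at 0.5 SD (80.6%). The FDR-corrected analysis in the same article has less.

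The direction is firm for Benjamini–Hochberg, apart from the limiting case of virtually identical tests that all carry true effects. The size is not fixed by the document. One-tailed at 51, it runs from a few points to more than 40 (38% with one true effect among 20 tests). If all 70 per group are retained, 80% can survive a small family or one with many true effects. A move to two-sided testing would be a further and separate loss, about 10 points at 51 before correction (80.6% to 70.6%).

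All of this assumes d = 0.5, the only effect that yields 51. It concerns the accuracy of a stated figure and does not show that the trial is too small.

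**What to change.** 1. **Sample size section:** say that the 80% at 51 per group is one-tailed and before FDR correction. Restate power, or the detectable difference, for the test that will be run, at both 51 and 70 per group. Show the number of tests, their correlation and the number of true effects as assumptions.
2. **Data analysis plan:** state the sidedness of the t-tests and make it agree with the Sample size section. If two-sided, the figures before FDR are about 71% at 0.5 SD, or 80% for 0.56 SD, with 51 per group, and 80% for 0.48 SD with 70.

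The cost is a few sentences and a less favourable power statement. Enrolment, outcomes and tests stay as planned.

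### The sample size section argues that larger structural equation models need fewer participants; for the planned use of SEM the relation runs the other way, so SEM should not be cited as a basis for n = 70

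*Protocol article*

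**What the plan says.** The Sample size section of the protocol article says that power for comparing well-nourished and wasted children was estimated in two ways, by Student's t-test and by SEM. The t-test gives a minimum of 51 per group (80% power, 5% level, one-tailed).

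For SEM it relies on a published study that "used a series of Monte Carlo simulations to estimate that 50–70 participants would suffice to evaluate functional connectivity in the brain". It describes those models as medium sized, with 7 latent variables, and continues: "the model size is inversely related with sample size. Therefore, larger models, like those in the present study, require fewer participants". Group sizes are then raised to 70 for dropout.

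The Data analysis plan section lists SEM as one of three model types and uses it for multivariate outcomes and relationships. It adds: "Model fit will be evaluated using descriptive fit indices such as the Comparative Fit Index (CFI) which work with relatively small sample sizes".

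The article does not give the number of latent variables or indicators in the planned models, or say whether they are fitted within groups or on pooled data.

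**The concern.** The SEM argument extrapolates from a 7-factor simulation to larger models and treats the extra size as lowering the required N. Each added latent variable brings loadings, residual variances and correlations or paths to estimate from the same children. At a fixed small N, that makes estimation harder and pulls CFI down even when the model is right.

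Two things are at stake. One of the two stated supports for the sample size does not support it. And the text tells analysts that adding latent variables costs nothing, in a data set that includes neurocognitive, metabolome, microbiome and genetic measures. That encourages oversized models, improper solutions and re-specification after seeing the data.

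**Working it through.** **1. The plan's own reproducible figure.** For the t-test, n per group = 2(z₀.₉₅ + z₀.₈₀)²/d². With d = 0.5: 2(1.645 + 0.842)²/0.25 = 49.5, so 50 by the normal approximation. The exact t calculation gives 50.15, so 51. The stated 51 therefore reproduces at 0.5 SD. (The section writes the difference as 2 SD, which would need 4 per group; that is a separate point.) The SEM figure of 50–70 cannot be reproduced, because the article gives no inputs for it.

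**2. Where the inverse relation is true.** N for 80% power of the RMSEA close-fit test (assumed 0.05 against 0.08, 5% level):

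| df | 24 | 168 | 329 | 360 | 528 |
|---|---|---|---|---|---|
| N | 375 | 94 | 63 | 59 | 48 |

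For this purpose a larger model does need fewer participants.

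**3. Parameter counts.** Assume k correlated factors with 3 indicators each. Free parameters q = 2(3k) + k(k − 1)/2, and df = 3k(3k + 1)/2 − q.

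- k = 7: q = 42 + 21 = 63; df = 231 − 63 = 168
- k = 10: q = 60 + 45 = 105; df = 465 − 105 = 360
- k = 12: q = 72 + 66 = 138; df = 666 − 138 = 528

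Children per parameter run from 70/63 = 1.1 down to 51/138 = 0.4.

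**4. CFI and improper solutions for correct models.** CFI = 1 − max(T − df, 0)/max(T₀ − df₀, T − df, 0), where T is the model chi-square and T₀ that of the independence model. Maximum-likelihood factor models were simulated with normal data, loadings 0.7 and factor correlation 0.3 (150 replicates per cell; 60 for 10 and 12 factors). All of these are assumptions.

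| Factors | Mean CFI, n = 51 | Mean CFI, n = 70 | CFI ≥ 0.90, n = 70 | Improper, n = 51 | Improper, n = 70 | Mean CFI, n = 210 |
|---|---|---|---|---|---|---|
| 3 | 0.967 | 0.974 | 94% | 9% | 2% | 0.993 |
| 5 | 0.936 | 0.963 | 92% | 18% | 6% | 0.992 |
| 7 | 0.885 | 0.939 | 79% | 39% | 8% | 0.991 |
| 10 | 0.766 | 0.871 | 27% | 77% | 28% | 0.983 |
| 12 | 0.668 | 0.814 | 2% | 88% | 38% | 0.981 |

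A separate simulation under the same assumptions gave mean CFI at n = 70 of 0.968, 0.931 and 0.874 with 4, 7 and 10 factors. Its improper-solution rates at n = 51 were lower (28% with 7 factors, 57% with 10), so those rates are less certain than the CFI values.

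**5. Sensitivity to loadings.** Mean CFI at n = 70 with 3, 7, 10 and 12 factors:

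- loadings 0.5: 0.942, 0.873, 0.745, 0.634
- loadings 0.85: 0.987, 0.969, 0.939, 0.905

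The direction is the same at every loading; the size varies greatly. Improper solutions also rise from 3 to 10 factors at every loading, though at 0.85 they do not rise further at 12 (20% and 12% at n = 51, on 40 replicates).

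**6. Pooling.** The followed cohort is 140 + 70 = 210. If each group fell to 51, the pool would be 3 × 51 = 153. At n = 140 and loadings 0.7, mean CFI is 0.972 with 10 factors and 0.957 with 12, with at most 2% improper. At n = 210 and loadings 0.5, it is 0.962 and 0.942, with 7% and 15% improper.

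**The case against.** The section is about power, and for power of an overall fit test both the direction and the 50–70 figure can be coherent: 7 factors with 4 indicators each (329 df) need N = 63. What the cited simulation measured cannot be seen here. This stands as far as it goes, but the article draws its conclusion without that limit, and its planned use of SEM is not an overall fit test.

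A reader might go further and infer that correct models will usually be rejected on CFI. The documents do not support that. The article sets no CFI cut-off and names CFI only as an example. At n = 70 with 7 factors, about a quarter or fewer of correct models fall below 0.90 (21% and 26% in the two simulations), and with loadings of 0.85 a 10-factor model reaches 0.90 in 93% of runs.

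A reader might also infer that path estimates will be uninterpretable. No structural paths were simulated. The SD of a factor correlation at n = 70 and loadings 0.7 rises from 0.105 (3 factors) to 0.146 (7) and is then flat (0.152 with 10, 0.147 with 12).

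Nor does it follow that every SEM in this trial is under-sized. The article never says that models are fitted within groups, and pooled models behave acceptably.

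Finally, the consequence for n is small: the t-test alone gives 51, raised to 70.

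**Conclusion.** The inference that larger models need fewer participants is wrong for the SEM the article plans, and it should not help to justify the sample size. The direction is firm: more parameters and lower CFI for correct models as factors are added, at every loading tried. The magnitudes are conditional. They assume 3 indicators per factor, factor correlations of 0.3, normal data and fitting within a group of 51–70, none of which the article states. This is a methodological overgeneralisation, not an arithmetic error, and it leaves n = 70 in place. It is worth correcting because it removes a false support and a false reassurance about model size.

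**What to change.** In Sample size, delete the clause asserting the inverse relation and the sentence that follows it, and stop naming SEM as a power basis, so that n = 70 rests on the t-test alone. In Data analysis plan, describe SEM as exploratory unless N is justified by simulating the model actually planned (latent variables, indicators, free parameters) for CFI, convergence and precision of paths. State that it is fitted on the pooled 210 children followed longitudinally, with group in the model; 10–12 factors are workable there at loadings of about 0.7 or more, so no fixed cap on factors is needed.

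The cost is wording in two sections, plus a simulation only if SEM is to be more than exploratory. Recruitment and conduct do not change. The downside is that SEM loses its claimed power support.
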